**7-10. Post-treatment**

There are no restrictions on post-treatment after discontinuation of treatment.

**8. Evaluation items**

**8-1. Primary endpoints**

**8-1-1. Phase Ia part**

1) Safety: maximum tolerated dose (MTD), dose-limiting toxicities (DLT), and type, frequency, and severity of adverse events

2) Pharmacokinetic study

**8-1-2. Phase Ib part**

1) Safety: Types, frequency, and severity of adverse events

2) Effects on elimination of regulatory T cells

**8-2. Secondary endpoints**

**8-2-1. Phase Ia part**

1) Regulatory T-cell elimination efficacy

2) Efficacy: tumor shrinkage, progression-free survival (PFS), overall survival (OS)

**8-2-2. Phase Ib part**

1） Efficacy: tumor shrinkage, progression-free survival (PFS), overall survival (OS)

2) Determination of recommended doses for Phase II trials and beyond

**8-3. Definition of evaluation items**

**8-3-1. Definition of primary evaluation items**

1) Phase Ia

(1) Safety

The maximum tolerated dose (MTD) and dose-limiting toxicity (DLT) will be determined, and the type, frequency, and severity of adverse events will be observed. The Common Terminology Criteria for Adverse Events (CTCAE) v4.0 Japanese translation of the JCOG version^13)^ will be used for grading adverse events. Adverse events will be graded according to CTCAE v4.0.

The MTD is defined as the dose at which the number of subjects who developed DLT during the period up to 28 days after the start of treatment with the investigational drug was 3 or more. However, if the MTD is not reached at any dose, 1.0 mg/kg shall be the dose that was found to be well tolerated.

The observation period for DLT will be up to 28 days after the start of study drug administration. Among adverse events for which a causal relationship to the investigational drug cannot be ruled out, the following events will be considered DLTs.

Grade is determined according to CTCAE v4.0.

① Hematologic toxicity of Grade 4 or higher lasting for more than 7 days^*1^.

*1 "Febrile neutropenia" is defined as Grade 3 or higher regardless of duration, and "Neutropenia" is defined as treatment with G-CSF even if it is Grade 3 or lower. Lymphocytopenia" and "CD4 lymphocytopenia" are excluded.

② Non-hematologic toxicity of Grade 3 or higher

Symptoms judged to be "injection-related reactions" ("fever," "headache," "pain," "pruritus," "allergic reaction/hypersensitivity," etc.) are defined as Grade 4 or higher DLT. In addition, only AST (GOT), ALT (GPT), ALP, total bilirubin, creatinine, and potassium should be included in the clinical examination.

③ Others

i) Toxicity that caused the scheduled administration of the investigational drug to exceed 2 weeks beyond the specified scheduled administration date due to a Grade 3 in any of the symptoms judged to be "infusion-related reactions" in 2).

ii) Toxicities other than the above that prevented administration of the study drug more than twice during the DLT observation period due to the same event.

(2) Pharmacokinetics

Pharmacokinetic parameters will be calculated from the plasma concentration of Mogamulizumab during repeated dosing of the study drug. To evaluate the plasma pharmacokinetics of Mogamulizumab during repeated dosing. Plasma Mogamulizumab pharmacokinetic parameters will be calculated from Cmax after the first, fifth and eighth doses, Ctrough after the first, fifth and seventh doses, AUC0-7 day after the first and eighth doses and t1/2, CL, Vss and MRT if possible. In addition, the accumulation rate during repeated dosing periods will be calculated. Pharmacokinetic parameters in plasma will be calculated using pharmacokinetic analysis software WinNonlin.

2) Phase Ib

(1) Safety

The type, frequency, and severity of adverse events will be observed. Adverse events will be judged according to CTCAE v4.0.

(2) Regulatory T-cell elimination effect

The ratio of CD25-positive and Foxp3-positive cells among CD4-positive T cells will be measured by FCM analysis. The CD4-positive rate among lymphocytes is also measured and converted to a ratio among lymphocytes to calculate the number of CD4-positive, CD25-strongly positive and Foxp3-positive cells.

The effect of regulatory T-cell removal is determined by comparing the number of CD4-positive, CD25-positive and Foxp3-positive cells to baseline.

**8-3-2. Definition of secondary evaluation items**

1) Phase Ia

(1) Efficacy in eliminating regulatory T cells

See "8-3-1. Definition of Primary Endpoints 2) Phase Ib”.

2) Tumor shrinkage effect

① Evaluation of RECIST

Tumor shrinkage effect is evaluated according to RECIST ver. 1.1.

② Variation of RECIST

In addition to the evaluation of RECIST, assuming that there is a time lag between the start of administration of the investigational drug and the onset of tumor shrinkage, an evaluation method that defines target lesions, non-target lesions, and new lesions as follows (hereinafter referred to as the "RECIST variant method") will be used (the different parts from RECIST (ver.1.1) are underlined). ).

i) Target lesion

The target lesion should be a measurable lesion of at least 10 mm in longest diameter (15 mm in shortest diameter for lymph nodes) at baseline. In addition, measurable lesions with a maximum diameter of 10 mm or greater (15 mm or greater for lymph nodes) and non-target lesions that have grown to a maximum diameter of 10 mm or greater (15 mm or greater for lymph nodes) that are newly observed after the start of treatment with the study drug will be evaluated in addition to target lesions. There is no limit to the number of target lesions. Target lesions are evaluated by comparing the sum of the longest diameter (shortest diameter for lymph nodes) to baseline and using the criteria for target lesions in RECIST (ver. 1.1).

ii) Non-target lesions

Non-target lesions are defined as lesions other than target lesions at baseline. After the start of treatment with the investigational drug, non-target lesions are defined as lesions excluding those non-target lesions observed at baseline that have increased to a maximum diameter of 10 mm or more (15 mm or more for lymph nodes in terms of short diameter) after the start of treatment with the investigational drug and are evaluated as target lesions. Non-target lesions will be evaluated using the criteria for non-target lesions in RECIST (ver. 1.1).

iii) New lesions

New lesions are defined as bone lesions, soft membrane lesions, ascites, pleural/pericardial effusions, cutaneous lymphangitis, pulmonary lymphangitis, abdominal masses not visible on imaging studies, cystic lesions, meningitis, and other unmeasurable lesions observed after the start of study drug administration. Lesions less than 10 mm in longest diameter (lymph nodes less than 15 mm in shortest diameter) are not considered as new lesions. Measurable lesions with a maximum diameter of 10 mm or more (15 mm or more for lymph nodes) that are newly observed after the start of treatment with the study drug will be evaluated as target lesions and will not be treated as new lesions.

Even if the criteria for PD are met by Week 12, if the trial is continued after Week 12, it will not be treated as PD at that time unless it is confirmed as PD by RECIST's variant method The date of confirmation of PD by RECIST's variant method shall be the date when PD is first confirmed beyond 12 weeks. However, if the first evaluation beyond 12 weeks was PD, the PD confirmation date shall be the date of the first PD backward in the evaluation period from that time, and if there is no PD in the backward evaluation period, the date of the first PD beyond 12 weeks shall be analyzed as the PD confirmation date.

③ Common to RECIST evaluation and RECIST variants

In cases where necessary examinations could not be performed due to rapid worsening of the disease, the date of PD confirmation shall be the date when the worsening of the disease is clinically evident; in cases where the patient died before PD is confirmed, regardless of the reason for death, the most recent hospital visit date specified in the study protocol shall be considered as the PD confirmation date.

For patients who are determined to have CR or PR, a central image evaluation should be performed.

<About the RECIST variant>

Tumor shrinkage will be evaluated using a variant of RECIST (ver. 1.1), which was developed based on the recommendations of the Cancer Vaccine Clinical Trial Working Group and referring to the Immune-related response criteria (irRC). This method is based on the idea that PD is acceptable and will be evaluated retrospectively, since there will be a time lag before the actual clinical effect is manifested in cancer immunotherapy. Based on this idea, in this clinical trial, even if the criteria for PD are met, the trial will continue, and if no clinical response is observed thereafter, the date will be retroactively determined to be PD. In addition, with regard to the determination of tumor shrinkage, even if a new measurable lesion is detected after the start of treatment with the investigational agent, if the tumor as a whole has shrunk, it is considered to indicate that the investigational agent has been effective. Therefore, in the variant of RECIST (ver. 1.1), measurable lesions with a minimum diameter of 10 mm (15 mm for lymph nodes) are defined as target lesions, and the sum of the longest diameter (shortest diameter for lymph nodes) is used to evaluate the target lesions. Measurable lesions with a maximum diameter of 10 mm or more (15 mm or more in short diameter for lymph nodes) that are newly observed after the start of treatment with the investigational drug will be evaluated as target lesions and will not be treated as new lesions. In RECIST (ver. 1.1), the number of target lesions is limited to a maximum of 2 lesions per organ, for a total of 5 lesions per organ. Therefore, it is assumed that the number of target lesions may exceed the number of target lesions specified in RECIST (ver. 1.1). Therefore, there is no limit on the number of target lesions.

(3) Progression-free survival

Progression-free survival (PFS) shall be defined as the period from the start date of the investigational drug administration to the date of PD confirmation during the study period. For patients who died before PD is confirmed, the date of PD confirmation shall be the date of the most recent hospital visit as specified in the study protocol, regardless of the reason for death.

(4) Overall Survival

Overall Survival (OS) is defined as the period from the start date of study drug administration to death from any cause. For patients who survived without confirmed death, the date of last confirmed survival shall be considered as the date of last confirmation of survival, and for patients who were lost to follow-up, the date of last confirmed survival shall be considered as the date of discontinuation.

2) Phase Ib

(1) Tumor reduction effect

See "8-3-2. Definition of Secondary Endpoints 1) Phase Ia".

(2) Progression-free survival

See "8-3-2. Definition of Secondary Endpoints 1) Phase Ia".

(3) Overall survival

See "8-3-2. Definition of Secondary Endpoints 1) Phase Ia".

(4) Determination of recommended doses for Phase II and beyond

Recommended doses for Phase II and beyond will be determined based on a comprehensive review of the safety and efficacy in eliminating regulatory T cells in Phase Ib.

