**9-4-3. CT and MRI**

Measurements will be taken at baseline and at Week 12. Thereafter, it will be performed every 12 weeks. It will also be performed every 12 weeks after discontinuation of the investigational drug if possible, and measurements will be taken at the time of discontinuation of the study.

The CT or MRI scan should be performed using the same model at each site and under the same imaging conditions for each subject as far as possible.

The cases judged as CR or PR by the RECIST method are objectively and uniformly judged by the Central Evaluation Committee of Imaging, which is a third-party organization.

The investigator submits the image data of cases judged as CR or PR to the Central Radiological Evaluation Committee at an appropriate time in accordance with the "Procedures for Central Radiological Evaluation," which is separately stipulated. If the judgment of the investigator and that of the Central Radiological Evaluation Committee differ, the judgment of the Central Radiological Evaluation Committee shall be the final evaluation.

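### Under the RECIST variant a Week 12 progression keeps its date only if a later evaluation confirms it, so patients without that evaluation can get a later PFS date or none

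*Protocol*

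**What the plan says.** Protocol 8-3-2 evaluates tumor response by RECIST 1.1 and, in parallel, by a variant that allows for delayed response. Under the variant, a PD met by Week 12 is suspended in patients who go on: "if the trial is continued after Week 12, it will not be treated as PD at that time unless it is confirmed as PD". The default date is then a later one: "The date of confirmation of PD by RECIST's variant method shall be the date when PD is first confirmed beyond 12 weeks". An exception restores the earlier date, and its trigger is "if the first evaluation beyond 12 weeks was PD". In that case "the PD confirmation date shall be the date of the first PD backward in the evaluation period from that time".

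Two rules common to both methods follow in 8-3-2. If rapid worsening makes the examinations impossible, "the date of PD confirmation shall be the date when the worsening of the disease is clinically evident". The death rule covers "in cases where the patient died before PD is confirmed, regardless of the reason for death, the most recent hospital visit date", which becomes the PD date; the PFS definition repeats it. PFS runs from first dose to the date of PD confirmation, without saying whether RECIST 1.1 or the variant supplies that date.

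The explanatory text on the variant, also in 8-3-2, gives the intent: "if no clinical response is observed thereafter, the date will be retroactively determined to be PD".

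Section 9-4-3 schedules CT or MRI at baseline, Week 12 and every 12 weeks after that. Off drug, "It will also be performed every 12 weeks after discontinuation of the investigational drug if possible"; the same sentence goes on to plan a scan when the patient discontinues the study.

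**The concern.** The backdating exception needs a later evaluation. The protocol does not say what happens to a Week 12 PD when there is none, so the death rule, the rapid-worsening rule or no rule at all takes over. A patient who progresses at Week 12 and dies before the next scan can then be credited with a longer PFS than one who progresses at the same scan and lives to have it confirmed. A patient who leaves alive and unscanned loses a documented progression.

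The variant exists to avoid penalizing delayed response, but none of these patients showed one. The protocol makes the situation foreseeable. Scans are 12 weeks apart, PD is a reason to stop drug only after Week 24 (7-7-3), and eligibility asks for only three months' expected survival (4-1). Study evaluation also ends when a patient withdraws consent or stops attending (14-1-2). What is at stake is the variant-based Kaplan-Meier PFS in both parts.

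**Working it through.** **Inputs**
- Scans at Week 12 and every 12 weeks after (9-4-3), so the next is at Week 24.
- First dose is Week 1 (9-1), so Week k falls 7 × (k − 1) days after first dose. Week 12 = 7 × 11 = 77, Week 16 = 7 × 15 = 105, Week 20 = 7 × 19 = 133, Week 24 = 7 × 23 = 161.
- Blood sampling every 4 weeks after Week 12 when possible (9-4-2), so visits may fall at Weeks 16 and 20.
- PFS estimated by Kaplan-Meier (11-4); 20 patients per Phase Ib group (7-6-2).

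The protocol gives no PFS figure or progression rate, so there is nothing to reproduce.

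**Step 1: apply the rules.** All patients below have PD at Week 12 and continue. PFS is dated by the variant.

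| What follows | Rule | PFS |
|---|---|---|
| PD again at Week 24 | backdating | day 77, event |
| Death, no protocol visit after Week 12 | death rule | day 77, event |
| Death, last visit Week 16 | death rule | day 105, event (105 − 77 = 28 days later) |
| Death, last visit Week 20 | death rule | day 133, event (133 − 77 = 56 days later) |
| Rapid worsening prevents examination | rapid-worsening rule | event when worsening is evident, after day 77 |
| Leaves alive, discontinuation scan shows PD | backdating | day 77, event |
| Leaves alive, no discontinuation scan, no rapid worsening | none | no PD date |

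A patient who does not continue after Week 12 keeps the Week 12 PD, because the set-aside applies only to those who continue.

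**Step 2: compare with the stated rationale.** The explanatory text makes PD retroactive when no response follows. No response was observed in any row, so that text points to day 77 throughout. The operative rules give day 77 in three of the seven rows.

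**Step 3: illustrate the effect on Kaplan-Meier.** Every count here is an assumption. Take 20 patients, P with PD at Week 12 and the other 20 − P with PD at Week 24. Of the P, X have no later evaluation: half die and half are censored, at Week 16 or 20.

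- Written rule: S(77) = 1 − (P − X)/20.
- Week 12 date stands: S(77) = 1 − P/20.
- Difference: X/20.

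With P = 10 and X = 2, the written rule gives S(77) = 1 − 8/20 = 0.60. One death among the 12 at risk on day 105 gives 0.60 × 11/12 = 0.55. The curve stays above 0.50 until day 161, so the median is 161 days. If the Week 12 date stood, S(77) would be 0.50 and the median 77 days.

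PFS at Week 12, with the median in days:

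| P | Week 12 date stands | X = 2 | X = 4 | X = 6 |
|---|---|---|---|---|
| 8 | 0.60, 161 | 0.70, 161 | 0.80, 161 | 0.90, 161 |
| 10 | 0.50, 77 | 0.60, 161 | 0.70, 161 | 0.80, 161 |
| 12 | 0.40, 77 | 0.50, 77 | 0.60, 133 | 0.70, 161 |
| 14 | 0.30, 77 | 0.40, 77 | 0.50, 77 | 0.60, 105 |

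Week 12 PFS rises by X/20 in every case. The median moves in some cases and not in others.

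**The case against.** The strongest reply is that several provisions narrow the gap. The rapid-worsening rule gives a dated event to patients too ill to be examined. The planned scan at study discontinuation, if done and positive, restores day 77. The explanatory text already states the retroactive intent. RECIST 1.1 runs in parallel and counts the Week 12 PD, and the PFS definition does not name the variant. PFS is secondary and has no test, the recommended dose rests on safety and regulatory T-cell removal, and detailed methods go to a separate analysis plan.

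Most of this stands as a limit on size, but it does not remove the defect. The rapid-worsening date still falls after Week 12. The discontinuation scan cannot help a patient who leaves without it. The explanatory text conflicts with the operative rule and so does not repair it. The death rule is stated twice in the protocol, so its result is fixed there and is not a detail left for later.

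A reader might infer more than the text supports:
- **That the sickest patients get the longest PFS.** Deaths are dated at or before their last visit, for example Week 16 or 20, while patients free of PD at Week 12 and progressing at Week 24 score day 161.
- **That every such death is dated later.** A death with no visit after Week 12 ties at day 77.
- **That every deterioration or withdrawal loses its event.** The rapid-worsening rule and the discontinuation scan cover some of them.

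**Conclusion.** The point holds, conditional on the variant supplying the PFS date. The rules can then give a later date after death or rapid worsening than after survival to a confirming scan, and they leave no PD date for a patient who goes unscanned. All three outcomes run against the section's own rationale.

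The individual shifts are exact given the visit assumed: 28 days for a last visit at Week 16 and 56 days for Week 20. The bias in variant-based Kaplan-Meier PFS is upward. Its size cannot be estimated, because the protocol gives no rate of Week 12 PD, of continuation, or of missing later evaluation; the 20-patient table only shows how the estimate responds. RECIST 1.1 results are unaffected. With no hypothesis test on PFS, this is a bias in a descriptive secondary estimate and not an error-rate problem. It should still be corrected, because the rule as written gives the wrong ordering and the repair is cheap.

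**What to change.** In Protocol 8-3-2, variant method, state that:
- a PD met by Week 12 is set aside only if a later evaluation shows non-PD;
- if there is no later evaluation for any reason, the first PD date stands;
- that date takes precedence over both the death rule and the rapid-worsening rule.

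In the PFS definition, state whether RECIST 1.1 or the variant supplies the PD date, and align the repeated death rule with the change.

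The cost is a few sentences and matching derivation code. No new data or visits are needed, and patient management does not change. The one downside is that variant PFS becomes slightly less favorable.

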**8-3-3. Other items defined**

1) Common to both Phase Ia and Phase Ib

(1) Antigen-specific antibody immunoreactivity test (NY-ESO-1 and XAGE-1b)

Antibody titers against NY-ESO-1 or XAGE antigens in serum are measured using recombinant NY-ESO-1 protein or synthetic XAGE protein by ELISA.

An IgG titer exceeding the mean of ELISA absorbance + 3 S.D. in healthy human serum is defined as positive, and an "increase" or "decrease" is defined as a change in the maximum dilution fold that shows positive results.

(2) Evaluation of regulatory T cells (optional)

Cell surface staining is performed using CD3, CD4, CD25, CD45RA, etc., which are markers of regulatory T cells. In addition, intracellular staining with transcription factor Foxp3, etc., and analysis using FCM. Among the regulatory T cells, the fraction with a strong inhibitory function that suppresses the anti-tumor immune response is accurately identified after careful removal of dead cells. Since this fraction strongly expresses CCR4, we will examine changes in this fraction upon administration of Mogamulizumab.

(3) Antigen-specific antibody immunoreactivity test (antigens other than NY-ESO-1 and XAGE-1b) (optional)

An ELISA using serum is performed to evaluate the enhancement effect of antigen-specific immune response. Measure the response to tumor antigens MAGE-A1, MAGE-A3, MAGE-A4, CT7/MAGEC1, CT10/MAGEC2, CT45, CT46/HORMAD1, SOX2, SSX2, p53 and other antigen proteins.

(4) Antigen-specific cellular immune response test (optional)

To evaluate the enhancement effect of antigen-specific immune response, antigen-specific CD4 and CD8 T cell responses are measured using peripheral blood. To observe the response to NY-ESO-1 and XAGE-1b, which are expressed 20-50% in the carcinoma of interest, CD4/CD8 T cells will be co-cultured with antigen-presenting cells to which NY-ESO-1 or XAGE-1b protein is added, and IFN-γ-producing cells will be detected by IFN-γ secretion assay.

(5) Evaluation of cytokine production (optional)

The effector cell side is affected by antigen stimulation due to changes in regulatory T cells induced by administration of Mogamulizumab, and the ability to produce multiple effector cytokines such as IL-2, TNF-α and IFN-γ is evaluated by intracellular staining. After antigen stimulation, cytokines are trapped intracellularly using transporter inhibitors, and the cell surface is stained with Live/Dead staining kit, anti-human CD3, CD4, CD8, CD45 antibodies, and fixed, and intracellularly stained with human IFN-γ antibody, human TNF-α antibody, human IL-2 antibody Intracellular staining with human IFN-γ, human TNF-α and human IL-2 antibodies, if necessary, clones of antigen-specific T cells will be established for HLA binding and epitope analysis. In addition, antigen-specific T cells will be monitored using tetramers.

6) Immunocompetent and regulatory cell analysis (optional)

Immunoregulatory cells such as regulatory T cells and MDSCs, helper T cell fractions (Th1, Th2, Th17), and the percentage of monocytes and dendritic cells are analyzed over time by FCM. In the analysis of immunosuppressor cells, regulatory T cells are stained with anti-human CD4, CD8, CD25, and CD45RA antibodies, and MDSCs are stained on the cell surface with anti-human CD3, CD11b, CD14, CD15, CD33, CD45 and HLA-DR antibodies.

The expression of immunoenhancing factors such as ICOS, OX-40, GITR, 4-1BB, and immunosuppressive factors such as PD-1, BTLA, TIM-3, 2B4, etc. are analyzed over time by FCM using the respective antibodies.

(7) Immunohistochemistry (optional)

Tissue biopsy specimens such as surgically removed tissues from the past or tissue biopsies obtained during endoscopic examinations as part of routine medical examinations will be used to determine the bio-distribution of immune-related cells. When possible, one or two additional biopsies should be obtained from the tumor site in addition to the biopsies normally required for diagnosis during endoscopic examination.

All specimens collected are used for pathological diagnosis at each institution. After diagnosis, unstained specimens are prepared from the stored blocks and analyzed for immune-related molecules by immunostaining.

(8) Gene analysis (optional)

In order to explore genomic biomarkers that may predict the clinical efficacy of mogamulizumab and the development of toxicity (autoimmune adverse events: skin rash, interstitial pneumonia, etc.), gene polymorphism analysis using DNA derived from peripheral blood mononuclear cells before the start of treatment and copy number analysis will be used for genome-wide association study (GWAS) using DNA derived from peripheral blood mononuclear cells before the start of treatment, and comprehensive expression analysis of miRNAs in serum.

